##### Exclusion criteria

Participants who meet any of the following criteria will be excluded: (1) CSU disease history or allergic constitution; (2) pregnant or lactating; (3) Hamilton anxiety scale score (HAMA) > 7 or Hamilton depression scale score (HAMD) > 7; (4) metal implants, fMRI examination contraindications like claustrophobia; (5) severe asymmetry of skull anatomical structure or apparent lesions detected while scanning; (6) unconscious or unable to express subjective symptoms independently.

### Randomization and blinding

Eligible patients will be randomly assigned to the acupuncture or sham acupuncture group at a 1:1 ratio. Statistical analysis will be performed using SPSS software (version 22.0) to generate random sequences with a random number table. The random distribution cards will contain random numbers, serial numbers, and groups, packed in opaque numbered envelopes. The envelope will be unsealed following study enrolment. Owing to the particularity of acupuncture research, it is difficult to blind the acupuncture operators. As such, fake acupuncture devices and separate treatment rooms will be used for each patient to blind them as much as possible. Moreover, the “three separations strategy” will be strictly adhered to by researchers, operators, and statisticians throughout the research process. Efficacy evaluation, data analysis, and statistics will be completed by third parties blinded to the groupings.

### Interventions

Patients in the acupuncture and sham acupuncture groups will receive treatment for 4 weeks, five times per week for the first 2 weeks, and three times per week for the next 2 weeks, for a total of 16 treatments. The acupuncture group will be treated with filiform needles (Huatuo brand, 0.25 × 40 mm), whereas the sham group will be treated with retractable blunt needles (AcuPrime brand, 0.25 × 40 mm). A Park sham device (PSD) (DONGBANG Acupuncture Inc.) will be used to achieve patient blinding in both groups. Acupuncturists with a doctor’s qualification certificate and more than 5 years of experience will complete the treatment sessions. Before the formal start of the study, we will conduct a unified training and assessment of related acupuncture operations.

#### Acupuncture group

The acupuncture group will be treated with “PSD + filiform needle” combined equipment. The acupoint selection plan refers to the Chinese textbook *Acupuncture and moxibustion Science* and expert opinions (30). Bilateral acupoints: LI11 (Quchi), SP10 (Xuehai), SP6 (Sanyinjiao), ST36 (Zusanli), ST25 (Tian Shu), and HT7 (Shenmen); single acupoint: CV12 (Zhongwan). The acupoint locations are shown in Figure 2. The patients will be placed in the supine position. The operator will remove the release paper from the PSD surface and insert the needle through the device with the needle tip exposed at the end. After disinfecting the acupoints and inserting the needles, the PSD will be fixed. After inserting the needle (20–40 mm, vertically), the lifting-thrusting method will be applied to induce and maintain the Deqi sensation (frequency: 60–90 times/min, amplitude: 3–5 mm). The needles will be retained for 30 min.

**Figure 2 fig2:**
[figure not shown]
Location of acupoints and non-acupoints. NA1: midpoint between the medial epicondyle of the humerus and the ulnar malleolus, on the ulnar margin. NA2: 1.2 cun beside CV12. NA3: 1 cun lateral to ST25, the midpoint of ST25 and SP15. NA4: inner anterior edge of the arm, at the junction of the deltoid and biceps. NA5: on the thigh, 0.8 cun medial to the midpoint of the line connecting the anterior superior iliac spine and the outer superior angle of basis patellae. NA6: 1 cun lateral to ST36, between the stomach and gallbladder meridian. NA7: 3 cun above the prominence of the lateral malleolus, between the stomach and gallbladder meridian.

#### Sham acupuncture group

The sham group will be treated with the “PSD + retractable blunt needle” combined equipment. Non-meridian and non-acupoint points will be selected (Figure 2). The retractable blunt needle has a hollow handle, and the needle tip is flat and blunt. Upon insertion, the body of the needle retracts into the hollow needle handle and does not penetrate the acupoints, remaining on the skin surface without causing deqi sensations. The needle will be retained for 30 min without needle manipulation. The remaining operating procedures will be performed in the same manner as that described for the acupuncture group.

### Outcome measures

#### Primary outcome measure

##### Urticaria activity score 7

The UAS7—a fundamental scale for evaluating urticaria symptoms (2)—assesses the number of wheals and degree of itching. Owing to the frequent and varying attacks of urticaria, we recommend daily recording. Subsequently, a total score of seven consecutive days will be used to evaluate urticaria activity.

#### Secondary outcome measures

##### Visual analog scale

The VAS will be used to evaluate the degree of urticarial itching in subjects over 1 week. More specifically, the participants will use a 10 cm horizontal line marked from 0 (no itching) to 10 (intolerable itching) to indicate their itching sensation. The degree of itching will be evaluated by measuring the distance from 0 to the mark. As CSU attacks occur more than once a day, the record is based on the highest daily VAS itching score.

##### Dermatology life quality index

The DLQI will be used to evaluate quality of life. This index covers six areas: symptoms and feelings, daily activities, leisure, work and school, interpersonal relationships, and the impact of treatment on everyday life (31).

##### Pittsburgh sleep quality index

The PSQI comprises nine questions used to evaluate the effect of CSU on sleep quality. The evaluation includes sleep quality, sleep latency, sleep duration, sleep efficiency, sleep disorders, sleeping pills, and daytime dysfunction (32).

##### Hamilton anxiety/depression scale

The Hamilton Anxiety Scale (HAMA) consists of 14 items (33), whereas the Hamilton Depression Scale (HAMD)_comprises 17 items (34). Both of these scales will be employed to evaluate the impact of CSU on the mental health of patients.

##### Self-rating anxiety/depression scale

The Self-rating anxiety scale (SAS) (35) and Self-rating depression scale (SDS) (36) are both self-report questionnaires consisting of 20 items each, designed to assess levels of anxiety and depression. Both have been widely used in mental health assessments among patients with various skin and other medical conditions (37).

#### Skin wheal measures

Infrared thermometers (Cofoe; Cofoe Medical Technology Co., LTD) will be used to measure the skin temperature of wheals. We will also use skin analyzers (RealBubee, Ningbo Realbubee Medical Equipment Co., LTD) to measure skin moisture, oil, and elasticity, as well as Vernier calipers to measure each wheal’s maximum length and vertical diameter. The arithmetic mean of the measured values will be recorded as the typical value.

### Serum laboratory testing

Patients with CSU exhibit higher levels of serum-specific IgE and C-reactive protein (CRP) compared to healthy controls (38, 39). Therefore, CSU patients will receive fasting hemospasia before and after treatment to detect serum-specific IgE and CRP levels.

### Gut microbiota collection

Stool samplers will be used to collect specimens from the middle of the stool (approximately 3 g) at the hospital. Samples will then be placed in a 10 mL centrifuge tube and immediately stored at −80°C. The genomic DNA of samples will be extracted by cetyltrimethylammonium bromide (CTAB) or sodium dodecyl sulfate (SDS) methods, while agarose gel electrophoresis will be employed to assess the purity and concentration of the extracted DNA. Subsequently, DNA will be collected in a centrifuge tube and diluted with sterile water to 1 ng/μL for further analysis.

### Skin microbiota collection

A sterile cotton swab soaked with normal saline will be applied to the skin surface (patients: skin at the wheals; healthy persons: corresponding normal skin). The sampling surface will be wiped smoothly in the horizontal and vertical directions, respectively. Subsequently, the bottom of the cotton swab head will be cut off at three sampling points, placed in a 15 mL centrifuge tube, and stored at −80°C. The DNA extraction and detection methods were the same as those for gut microbiota collection.

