## Methods and analysis

### Study design

This is a parallel randomized sham-controlled functional neuroimaging study. Fifty CSU patients and 25 matched healthy subjects will be randomly assigned to the verum or sham acupuncture groups at a 1:1 ratio. The total observation period of this study is 6 weeks, including a baseline period of 2 weeks and a clinical treatment period of 4 weeks. Before treatment, all participants (*n* = 75) will undergo clinical index evaluation, magnetic resonance scanning, and microflora collection. Following treatment, only the CSU patients will be reassessed for these indicators. The study flow chart is presented in Figure 1, and the schedule of enrolment, interventions, and assessments is shown in Table 1. This trial will be reported following the Standard Protocol Items: Recommendations for Interventional Trials (SPIRIT).

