**Assessments**				
UAS7/VAS		√	√	√
PSQI/DLQI		√	√	√
HAMA/HAMD		√	√	√
SAS/SDS		√	√	√
Skin wheal measures		√	√	√
IgE/CRP		√		√
fMRI		√		√
Gut/skin microbiota		√		√

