### Participants

#### CSU patients

##### Diagnosis criteria

According to the diagnostic criteria of CSU in “the International EAACI/GA^2^LEN/EuroGuiDerm/APAAACI guidelines for the definition, classification, diagnosis, and management of urticaria” (2021 edition) (2): (1) repeat appearance of wheals, (2) with/without angioedema, (3) wheal episodes ≥2 times per week, (4) recurrent attacks ≥6 weeks, and (5) spontaneous wheals induced by nonspecific stimulation factors.

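### Skin swabs, wheal temperature and wheal size are tied to a wheal being present, so follow-up skin data can be missing or non-comparable in relation to treatment response

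*Protocol article*

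**What the plan says.** Under Skin microbiota collection, the swab is taken at a site defined by the lesion: "patients: skin at the wheals; healthy persons: corresponding normal skin". No other site is named for patients.

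Under Skin wheal measures, infrared thermometers "will be used to measure the skin temperature of wheals". Skin analyzers are used "to measure skin moisture, oil, and elasticity, as well as Vernier calipers to measure each wheal’s maximum length and vertical diameter". The summary rule is: "The arithmetic mean of the measured values will be recorded as the typical value". Temperature and size are thus explicitly wheal measurements. Moisture, oil and elasticity sit under the same heading, but the sentence gives no site for them.

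Table 1 schedules "Skin wheal measures" at weeks 0, 2 and 4 and "Gut/skin microbiota" at weeks 0 and 4. Study design adds: "Following treatment, only the CSU patients will be reassessed for these indicators".

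The primary outcome, UAS7, counts wheals as well as itch. The Microbiota analysis section compares community structure between CSU patients and healthy people and between the two acupuncture arms. The Correlation analysis section relates microbiota to connectivity and clinical indicators and compares the coefficients between arms.

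**The concern.** The measurement site depends on something the treatment is meant to remove. If a patient has no wheal at week 4, the written rules give no place to swab or take temperature, and a mean over no wheals is undefined rather than zero. If wheals remain but have moved, the week 4 swab comes from a different body site than the week 0 swab, so a change in flora mixes treatment with location. If staff swab clear skin instead, the change mixes treatment with lesional versus non-lesional skin, and different staff may choose differently.

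Whether a usable value exists, and what kind of skin it comes from, is therefore related to a component of the primary outcome. Should acupuncture clear more wheals than sham, usable skin data would be lost or altered unequally between the arms after randomisation. The skin part of the arm comparison and of the correlation network would then describe a group partly selected by response. Week 4 samples that were not taken cannot be recovered later.

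**Working it through.** **1. Following the text for three kinds of patient at week 4**

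| Patient at the visit | Swab | Wheal temperature | Mean diameter |
|---|---|---|---|
| Wheals at the week 0 site | comparable | comparable | defined |
| Wheals only at another site | different body site | different body site | defined |
| No wheals | no qualifying site | undefined | undefined (mean over no values) |

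**2. Can a visit be wheal-free?** Yes. The diagnostic criteria ask only for "wheal episodes ≥2 times per week", and entry needs a 7-day UAS7 above 14. Neither requires a wheal on the visit day. Wheals may therefore be absent at week 0 or 2 as well; absence at week 0 is not caused by treatment, absence later may be.

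**3. Loss of numbers (assumed clearance rates).** The Sample size section gives 50 patients, so 25 per arm, and no effect size or power. With assumed wheal-free proportions, n per arm = 25 × (1 − proportion). Power for an arbitrary 0.8 SD difference at two-sided 0.05 is Φ(0.8/√(1/n₁+1/n₂) − 1.96).

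| Wheal-free, acupuncture / sham | n₁ / n₂ | Power |
|---|---|---|
| 0% / 0% | 25 / 25 | Φ(0.8/0.283 − 1.96) = 81% |
| 20% / 10% | 20 / 22.5 | Φ(0.8/0.307 − 1.96) = 74% |
| 30% / 10% | 17.5 / 22.5 | Φ(0.8/0.319 − 1.96) = 71% |
| 40% / 20% | 15 / 20 | Φ(0.8/0.342 − 1.96) = 65% |
| 50% / 20% | 12.5 / 20 | Φ(0.8/0.361 − 1.96) = 60% |

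**4. Selection, wheal diameter only (all inputs assumed).** Let baseline diameter have mean 12 and SD 5 mm, and the reduction SD 5 mm, floored at 0. Before flooring, week 4 diameter is normal with mean μ = 12 − reduction and σ = √(25+25) = 7.07. Then:
- wheal-free proportion = Φ(−μ/σ)
- mean with zeros kept = μΦ(μ/σ) + σφ(μ/σ)
- mean among those with wheals = that value / Φ(μ/σ)

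For a reduction of 8 mm, μ = 4: wheal-free 28.6%; mean 4 × 0.714 + 7.07 × 0.340 = 5.26; wheals only 5.26/0.714 = 7.37. For 3 mm, μ = 9: wheal-free 10.2%; mean 9 × 0.898 + 7.07 × 0.177 = 9.34; wheals only 10.40.

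| Reduction, acupuncture vs sham (mm) | Difference, zeros kept | Difference, wheals only | Attenuation |
|---|---|---|---|
| 8 vs 3 | 4.08 | 3.03 | 26% |
| 6 vs 2 | 3.47 | 2.67 | 23% |
| 4 vs 2 | 1.80 | 1.42 | 21% |
| 8 vs 4 | 3.20 | 2.34 | 27% |

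Simulation of the same model gives the same attenuation.

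**5. A generic skin outcome (also assumed).** Let latent severity be N(0,1) in sham and lower by 0.5 or 0.8 SD with acupuncture, with wheals present only above a threshold that clears 10 to 30% of sham patients. That clears 22 to 61% of acupuncture patients. For an outcome linearly related to severity (correlation 0.3 to 0.7), the difference among those with wheals is 36 to 61% smaller than in all randomised patients; for example −0.25 becomes −0.13.

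Steps 4 and 5 show that the mechanism works and that its size depends heavily on the model. Neither models community composition, so neither estimates the bias in the flora analyses.

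**The case against.** The strongest reply is that the article nowhere says that patients without wheals are dropped or left unsampled. Study design has CSU patients reassessed after treatment, and a fallback site or a rule for scoring absent wheals may stand in the full protocol, an operating procedure or the case report form. That stands as a limit: the article shows that no valid sample is specified, not that data will be lost. It does not dispose of the point, because the article does state a site rule, and that rule depends on the lesion.

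Several stronger readings are tempting and are not supported:

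- **That only non-responders are compared.** Patients with fewer or smaller wheals can still be swabbed and measured. In the 8 versus 3 mm illustration, about 71% of the acupuncture arm still has wheals.
- **That the randomised comparison is lost.** It can be biased, but the same illustration keeps about three quarters of the difference. Wheals also come and go from day to day, so absence at a visit is only partly a matter of response.
- **That all skin measures are taken only at wheals.** For moisture, oil and elasticity this rests on a heading alone.
- **That more data must be lost in the acupuncture arm.** This presupposes that acupuncture works better than sham.
- **That the main results are undermined.** UAS7 is a daily diary score. It, fMRI, gut flora and serum markers do not depend on a wheal at the visit, and the week 0 comparison with controls precedes treatment.

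The article already provides for corresponding sites in controls, so nothing is missing there.

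**Conclusion.** The point holds for week 4 skin flora and for wheal size and wheal temperature at weeks 2 and 4, together with the arm comparisons and correlations that use them. Under the written rules these data can be missing, or come from a different kind or place of skin, in relation to response.

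The size cannot be derived from the article. Under assumed inputs, the wheal-diameter difference shrinks by 21 to 27%, a generic severity-related outcome by 36 to 61%, and power for an assumed 0.8 SD difference falls from 81% to between 60 and 74%. In these models the bias is towards no difference. For real flora data both direction and size are unknown.

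This should be fixed, as a defect in secondary and exploratory skin outcomes; it does not threaten the primary outcome or the imaging.

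**What to change.** - **Swab.** Record the swab site or sites at week 0 and swab the same ones at week 4 in every CSU patient, wheal or no wheal. State which site to record if no wheal is present at week 0.
- **Flag.** Record wheal present or absent at each swab, for description only. Using it to define the analysis set would bring the selection by response back.
- **Wheal size.** Keep measuring wheals wherever they occur. Score size 0 only when the patient has no wheal anywhere at that visit. Scoring 0 because the week 0 site is clear would create false clearance when new wheals lie elsewhere.
- **Temperature.** Also take it at the recorded week 0 site. State the site for moisture, oil and elasticity.
- **Analysis.** Compare all randomised patients, and keep wheal-only results as descriptive.

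The cost is a few lines in the sampling procedure, site and flag fields in the case report form and one further temperature reading, with no extra swabs. The downside is that some week 4 swabs will come from non-lesional skin, so change within a patient includes resolution of the lesion. The between-arm comparison at the same recorded sites nevertheless keeps all randomised patients.

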### fMRI outcome measures

We will use a Siemens’ 3.0 T superconducting magnetic resonance scanner and a 12-channel head coil for magnetic resonance scanning. All subjects will be scanned with the same parameters, and the same operator will be responsible for routine operations. An operator instruction manual will be produced to standardize the operation process and communication with the subjects. The various factors that can impact the magnetic resonance scanning (MRS) process will be strictly regulated. That is, the scanning time will be unified and the interference of the environment, equipment, technicians, and psychology on the subjects’ brain function imaging data will be limited, improving data reliability. The scanning parameters will be as follows: repetition time (TR): 2,000 ms, echo time (TE): 30 ms, field of view (FOV): 240 × 240 mm^2^, slice thickness (ST): 4 mm, number of slices (NOS): 40, matrix: 64 × 64, flip angle (FA): 90°.

### Safety assessment

If adverse events, such as dizziness, pain, bleeding, or haematoma occur after acupuncture, researchers will deal with them in a timely manner by inviting expert to consult when necessary to ensure the safety of the participants. The event’s occurrence time, symptoms, signs, severity, duration, and treatment methods will be recorded in the report forms and analyzed. The ethics committee will then evaluate whether the trial should be suspended.

### Sample size

Due to the particularity of the neuroimaging mechanism, the clinical sample calculation method is not applicable. According to fMRI sample size research, each group should include at least 6–12 patients (40), while the statistical data of 20 subjects resembles that of large sample data for 130 subjects (41). Considering the uncertain factors in this study, including the loss or elimination of subjects and unavailable data due to head movements, we included 50 patients and 25 matched healthy persons in this study.

### Statistical analysis

#### Clinical data analysis

All baseline and clinical response index data will be analyzed using the SPSS software (version 22.0). Measurement data will be expressed as mean ± SD. Following the normality test, an independent samples *t*-test will be used if the criteria of normal distribution and homogeneity of variance are met. Otherwise, a non-parametric test (Mann–Whitney U-test) will be used. Count data will be analyzed by the two-sided χ^2^ test. A *p* < 0.05 will be considered significant.

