##### Inclusion criteria

The study will enroll patients who meet the following criteria (1) meet the diagnostic criteria of CSU as defined in “The international EAACI/GA^2^LEN/EuroGuiDerm/APAAACI guideline for the definition, classification, diagnosis, and management of urticaria” (2); (2) right-handedness of either sex, aged between 18 and 70 years, with a minimum of 6 years of education; (3) urticaria activity score 7 (UAS7) > 14; (4) no metal implants, no fMRI scanning contraindications; (5) patients who have not taken any antihistamines within 2 weeks before entering the study, and have not used steroid hormones or immunosuppressants within the last month; (6) no acupuncture treatment within 3 months before entering the study, no participation in other ongoing clinical studies; (7) and patient who have provided signed informed consent and volunteered to participate in this study.

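### The primary UAS7 comparison makes no covariate adjustment for the baseline UAS7 that the trial collects, which costs precision at 25 per arm unless baseline and week 4 scores are almost uncorrelated

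*Protocol article*

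**What the plan says.** The Clinical data analysis section of the Protocol article covers all baseline and clinical response indices. For measurement data it names two tests. The independent-samples t-test "will be used if the criteria of normal distribution and homogeneity of variance are met". "Otherwise, a non-parametric test (Mann–Whitney U-test) will be used". No covariate or model is named.

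UAS7 is the primary outcome: "a total score of seven consecutive days will be used to evaluate urticaria activity". Table 1 schedules it at weeks 0, 2 and 4. It is also an entry criterion, "urticaria activity score 7 (UAS7) > 14", so every randomised patient should have a pre-treatment value. Neither the outcome section nor the analysis section says which post-baseline visit is primary, or whether the tested variable is the score or its change from week 0.

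On numbers, the Sample size section states that "we included 50 patients and 25 matched healthy persons in this study", and Randomization and blinding states "Eligible patients will be randomly assigned to the acupuncture or sham acupuncture group at a 1:1 ratio". That gives 25 patients per arm before losses.

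**The concern.** A baseline measurement of the primary outcome is usually the strongest available predictor of its later value. A t-test on week 4 scores leaves all between-patient variation in starting UAS7 in the error term. A t-test on change scores uses the baseline, but with a fixed coefficient of one instead of the coefficient the data support. ANCOVA estimates that coefficient.

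With 25 per arm, and a sample size not derived from any clinical effect, the plan has no stated power margin to absorb the loss. The choice between t-test and Mann–Whitney also depends on pre-tests of the trial's own data. Whether the primary result is a difference in means or a rank comparison is therefore not settled beforehand.

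**Working it through.** **Inputs.** From the article: 25 per arm (50 patients, 1:1) and a significance level of 0.05. Two-sided is stated there only for the chi-square test and is assumed here for the t-test. Also assumed: 80% power, and a baseline to week 4 correlation, rho, of 0 to 0.7. Effects are in units of the week 4 UAS7 SD. The article gives no effect size, SD, power or dropout rate, so it has no figure of its own to reproduce.

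**Unadjusted t-test on week 4 scores.** The standard error is √(2/25) = 0.283 SD. The normal approximation gives (1.960 + 0.842) × 0.283 = 0.79 SD. The exact noncentral t calculation with 48 degrees of freedom gives 0.809 SD. Power at a true difference of 0.5 SD is 41.0%.

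**Variance of the treatment effect relative to that test.**
- ANCOVA: 1 − rho², multiplied by 1 + 1/(2 × 25 − 4) = 1.022 for estimating the slope, with 47 degrees of freedom.
- Change-score t-test: 2(1 − rho), taking equal SDs at baseline and week 4.

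Example at rho 0.5: 0.809 × √0.75 = 0.700, and × √1.022 gives 0.708 SD for ANCOVA. For the change score, 0.809 × √1.0 = 0.809 SD.

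| rho (assumed) | Variance factor, ANCOVA (before the 1.022) | Variance factor, change score | Detectable SD, ANCOVA | Detectable SD, change score | Power at 0.5 SD, ANCOVA | Power at 0.5 SD, change score |
|---|---|---|---|---|---|---|
| 0 | 1.00 | 2.0 | 0.82 | 1.14 | 40.3% | 23.2% |
| 0.3 | 0.91 | 1.4 | 0.78 | 0.96 | 43.5% | 31.0% |
| 0.5 | 0.75 | 1.0 | 0.71 | 0.81 | 50.7% | 41.0% |
| 0.7 | 0.51 | 0.6 | 0.58 | 0.63 | 67.0% | 60.9% |

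**Patients per arm that the planned t-test would need to match ANCOVA with 25** (variance ratio only, leaving out the 1.022).
- Week 4 scores, 25/(1 − rho²): 25.0, 27.5, 33.3 and 49.0 at rho 0, 0.3, 0.5 and 0.7.
- Change scores, 25 × 2(1 − rho)/(1 − rho²) = 50/(1 + rho): 50.0, 38.5, 33.3 and 29.4.

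**Where ANCOVA stops helping.** Against the week 4 score, ANCOVA detects 0.814 SD at rho 0.1 and 0.801 SD at rho 0.2, compared with 0.809 SD unadjusted. The crossover lies between those two values.

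**Unequal SDs.** If the baseline SD is k times the week 4 SD, the change-score factor is 1 + k² − 2·rho·k. Subtracting 1 − rho² leaves (k − rho)², which is never negative. Apart from the small 1.022 factor, the change score cannot beat ANCOVA, and equals it only at k = rho.

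**Losses.** If 20 per arm remain (assumed), the unadjusted week 4 test detects 0.91 SD and ANCOVA at rho 0.5 detects 0.80 SD.

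**The case against.** The strongest reply has three parts. First, the size of the gain rests on a correlation that the article does not give. Requiring a UAS7 above 14 at entry narrows the baseline range and may lower it. At rho 0.3 the gain over the week 4 score is only 0.78 against 0.81 SD. Second, the article does not exclude a change-score test, which already uses baseline; at rho 0.7 ANCOVA's advantage over it is then 29 per arm, not 49. Third, the stated objective is the brain-network mechanism, and the sample was deliberately not sized on a clinical endpoint. All three stand as limits on the size. None favours the planned test, because ANCOVA is better than either version except against the week 4 score at very low rho, where the difference is trivial.

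A reader might infer more, and the document does not support it:
- **That the unadjusted test is biased.** Patients are randomised, so both the week 4 and the change-score comparison are unbiased over randomisation. A chance baseline difference adds error to the realised estimate; it does not invalidate the test.
- **That adjustment is free.** It costs one degree of freedom.
- **That weeks 2 and 4 will each be tested as primary at 0.05.** The article names no primary visit, but does not say this either.
- **That sparse counts will give false significance.** "Count data will be analyzed by the two-sided" chi-square test, the section says, but it does not say whether a continuity correction applies, and no responder outcome is defined. A small-count rule is commonly left to the SAP.

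**Conclusion.** The point holds as one of efficiency, not validity. The plan fixes tests for its primary outcome that take no covariate, although the baseline value is collected for every patient.

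Compared with a t-test on week 4 scores, ANCOVA makes little difference at rho 0.3 and a material one from about 0.5. Compared with a t-test on change scores, the gain is largest at low rho and shrinks as rho rises. The only region in which ANCOVA loses is against week 4 scores at rho of about 0.1 or less, by less than 0.01 SD in the detectable effect.

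These figures assume two-sided testing, 80% power, no losses, equal baseline and week 4 SDs for the change-score results, and randomisation of patients only. Study design also describes the healthy subjects as randomised, which conflicts with Randomization and blinding and needs reconciling. The calculations are for the t-test; the Mann–Whitney branch was not quantified, but it too takes no covariate.

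**What to change.** In Clinical data analysis, make the primary analysis an ANCOVA of week 4 UAS7 on arm and week 0 UAS7, reported as the adjusted mean difference with its 95% confidence interval. Name week 4 as the primary visit. Apply the same model to the other scales measured at baseline (VAS, DLQI, PSQI, HAMA, HAMD, SAS, SDS). Remove the rule that selects the test by normality and equal-variance pre-tests, and keep a rank-based comparison as a sensitivity analysis.

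This changes wording only. It needs no new data, visits or patients. The statistical price is one degree of freedom.
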